  - 580 ❖ CT scan or cervicofacial MRI (*The choice between MRI and CT is left to the*
  - 581 *discretion of the investigator but follow-ups must be carried out with the same*
  - 582 *technique*)
  - 583 ❖ Chest CT scan (*The use of PET-FDG is left to the choice of the investigators in each*
  - 584 *center if it is medically indicated*)
- 585 • EORTC QLQ-C30 and H&N35 questionnaire to be completed at **12 months and 24 months,**
- 586 in the absence of local, locoregional or distance progression.
- 587

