### 588 ***VI.5.3 Follow-up on recidivism***

- 589 In the event of local, regional, locoregional or distant recurrence, patients will be monitored only for
- 590 their vital status.
- 591 Data from salvage treatments will be collected in the CRF.
- 592

Table 1: Flow chart

| PERIODE DE L'ESSAI                                                                                                                                                                                                                                                                                                                                                                                                                   | BILAN A L'INCLUSION                  | SUIVI PENDANT LA RADIOTHERAPIE |       | VISITES DE SUIVI POST RADIOTHERAPIE STEREOTAXIQUE |            |                  |                                |                 |                   |                   |                   |                   |                   |
|--------------------------------------------------------------------------------------------------------------------------------------------------------------------------------------------------------------------------------------------------------------------------------------------------------------------------------------------------------------------------------------------------------------------------------------|--------------------------------------|--------------------------------|-------|---------------------------------------------------|------------|------------------|--------------------------------|-----------------|-------------------|-------------------|-------------------|-------------------|-------------------|
| Visites n°                                                                                                                                                                                                                                                                                                                                                                                                                           | V0                                   | V1                             | V2    | V3                                                | V4         | V5               | V6                             | V7              | V8                | V9                | V10               | V11               | V12               |

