### 670 **VI.9. Quality of life assessment**

671 Quality of life (QoL) is assessed by the European *Organisation for Research and Treatment of Cancer*  
672 (*EORTC*) questionnaires QLQ-C30 and QLQ-H&N35, French version.

673 The QLQ-C30 questionnaire (*Appendix 3*) is a cancer-specific questionnaire that consists of 30  
674 questions. Twenty-four questions participate in 9 multi-item scales: 5 functional scales (physical,  
675 role/position, cognitive, emotional, social), 3 symptom scales (fatigue, nausea/vomiting, pain) and  
676 one global condition scale. The remaining six questions are single-item scales assessing symptoms  
677 (dyspnea, insomnia, loss of appetite, constipation, diarrhea) and financial difficulties.

678 The QLQ-H&N35 questionnaire (*Appendix 3*) is a specific questionnaire for patients who have ENT  
679 cancer that consists of 35 questions. Twenty-four questions participate in 7 multi-item scales that  
680 assess ENT pain, swallowing, senses (taste and smell), speech, eating in society, social contacts and  
681 sexuality. The remaining 11 questions are uni-item scales describing specific concerns of patients  
682 with ENT cancer (dentition, mouth opening, dry mouth, sticky saliva, coughing, feeling unwell,  
683 taking painkillers, nutritional supplements, feeding tube, weight loss or gain).

684 The moments of collection of the quality of life questionnaires are:

- 685 • At the inclusion visit, i.e. after informed consent has been obtained and before the start of
- 686 stereotactic radiotherapy
- 687 • At the 30±5-day follow-up visit after stereotactic radiotherapy
- 688 • At the follow-up visit 12 months±10 days after stereotactic radiotherapy
- 689 • At the 24-month follow-up visit±10 days post-radiotherapy

690

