### 906 IX.2. Data analysis: general

907 Patients will be described and compared between groups at baseline according to the following  
908 variables:

- 909 • Compliance with eligibility criteria
- 910 • Epidemiological characteristics
- 911 • Clinical and treatment characteristics.

912 A description of the deviations from the protocol, the patients distributed according to these  
 913 deviations and the causes of abandonment will also be carried out. The number of patients included  
 914 and the curve of inclusions will be presented by groups.

915 Continuous variables will be presented as a mean and standard deviation, subject to the normality of  
 916 their distribution (Shapiro-Wilk test if necessary). In case of non-normality, they will be presented in  
 917 the form of median, quartiles and extreme values. The qualitative variables will be expressed in terms  
 918 of numbers and associated percentages. 95% confidence intervals (95% CI) will be reported. For each  
 919 variable, the number of missing data will be specified. Graphical representations will be associated  
 920 with these analyses as much as possible.

921 The estimate of the theoretical follow-up time will be the time difference between the date of inclusion  
 922 and the date of the database freeze. The follow-up will also be estimated according to the reverse  
 923 Kaplan Meier method for the observed follow-up. The parameters related to the time to events (SSR,  
 924 OS...) as well as the time to deterioration of quality of life (scores) will be estimated according to the  
 925 Kaplan-Meier method and described with a median confidence interval and rates at defined periods.  
 926 Patients without specific events at the time of study termination (baseline freeze of study data) will  
 927 be censored, for the "time to events" criteria, as of the date of the last update. Possible comparisons  
 928 between independent groups will consider the log-rank test (univariate analysis) and the Cox model  
 929 (multivariate analysis).

930 Tests will be bilateral, and a  $p < 0.05$  value will be considered statistically significant. As this trial  
 931 is exploratory, the adjustment of the risk of error of the first kind will not be proposed systematically,  
 932 but on a case-by-case basis in view of clinical and not only statistical considerations (48).

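### Time to quality-of-life deterioration carries the generic last-update censoring rule although questionnaires stop at recurrence, so on the natural reading the 12- and 24-month deterioration rates come out too low

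*Protocol*

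**What the plan says.** Protocol IX.2 names the time-to-event parameters, giving recurrence-free survival (SSR) and overall survival (OS) as examples. It then adds the QoL endpoint, "as well as the time to deterioration of quality of life (scores) will be estimated according to the" Kaplan-Meier method, with a median and rates at defined periods. The censoring rule follows: "Patients without specific events at the time of study termination (baseline freeze of study data) will" be censored, for the time-to-event "criteria, as of the date of the last update". No other section gives a censoring date for QoL.

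QoL collection is set out elsewhere:

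- VI.9 schedules questionnaires at inclusion, then "At the 30±5-day follow-up visit after stereotactic radiotherapy", then "At the follow-up visit 12 months±10 days after stereotactic radiotherapy", and again at 24 months.
- VI.5.2 asks for the 12- and 24-month forms only "in the absence of local, locoregional or distance progression".
- VI.5.3 says what happens afterwards: "In the event of local, regional, locoregional or distant recurrence, patients will be monitored only for" vital status. The footnote to Table 1 repeats this.

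IX.4 sets 10 points as the smallest clinically meaningful QoL difference, with 5 points in a sensitivity analysis. It does not say whether recurrence or death counts as deterioration.

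**The concern.** A QoL deterioration can be recorded only on a completed questionnaire. Once a patient recurs, questionnaires stop but vital-status updates continue. Take a patient who is stable at day 30, recurs at month 6 and is known to be alive at month 26. Under the last-update rule that patient is in the 12- and 24-month risk sets as not deteriorated, with no form after day 30.

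This is not occasional missing data. It follows from combining the collection schedule with the censoring rule. The patients affected have recurred and may be receiving salvage treatment, so they are poor candidates for being counted as stable. The trial has a single arm, so there is no comparator in which the error might cancel.

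**Working it through.** The protocol gives no figure for this endpoint, so there is none to reproduce. The check compares two censoring rules:

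- **Rule A:** event-free patients are censored at the last update, taken to fall after the 24-month visit.
- **Rule B:** event-free patients are censored at the last completed questionnaire.

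**Inputs from the protocol.** Post-baseline questionnaires fall at day 30, 12 months and 24 months (VI.9). The last two are collected only without progression (VI.5.2). IX.1 plans on 80 to 90% local control at two years, that is 10 to 20% local failure. Regional and distant recurrence come on top.

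**Assumptions not in the protocol.**

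- The deterioration probability is d at day 30, then h at each later visit among assessed patients. Low rates: d = 0.20, h = 0.15. High rates: d = 0.40, h = 0.30.
- Cumulative recurrence is r12 by 12 months and r24 by 24 months.
- Recurrence is independent of QoL.
- There are no deaths, and all forms that are due are completed.

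**Formulas.** Under rule A nobody leaves the risk set before 24 months, so the Kaplan-Meier estimate equals the simple proportion with a recorded event:

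F_A = d + (1 − d) × [(1 − r12)h + (1 − r24)(1 − h)h]

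Under rule B the hazard at each visit is h among those assessed:

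F_B = 1 − (1 − d)(1 − h)²

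**Worked case: low rates, r12 = 0.10, r24 = 0.20.**

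- 12-month hazard under A: 0.90 × 0.15 = 0.135, against 0.15 under B.
- 24-month hazard under A: events 0.80 × 0.85 × 0.15 = 0.102; risk set 0.90 × 0.85 + 0.10 = 0.865; ratio 0.118, against 0.15 under B.
- F_A = 0.20 + 0.80 × (0.135 + 0.102) = 0.390.
- F_B = 1 − 0.80 × 0.7225 = 0.422.
- Shortfall at 24 months: 3.2 points.

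**24-month deterioration rate over the range:**

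| r12 / r24 | Low rates: A vs B | Gap (points) | High rates: A vs B | Gap (points) |
|---|---|---|---|---|
| 5% / 10% | 40.6% vs 42.2% | 1.6 | 68.4% vs 70.6% | 2.2 |
| 10% / 20% | 39.0% vs 42.2% | 3.2 | 66.3% vs 70.6% | 4.3 |
| 20% / 35% | 36.2% vs 42.2% | 6.0 | 62.6% vs 70.6% | 8.0 |
| 25% / 40% | 35.1% vs 42.2% | 7.1 | 61.1% vs 70.6% | 9.5 |

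A Monte Carlo check with 200,000 patients per scenario and exponential recurrence gave gaps of 1.7 to 9.2 points.

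**At 12 months** the gap is (1 − d) × h × r12. It runs from 0.80 × 0.15 × 0.05 = 0.6 points to 0.60 × 0.30 × 0.25 = 4.5 points.

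**Direction.** Unassessed patients enter the denominator and never the numerator. The hazard at each visit is multiplied by the share of the risk set still assessed, so the sign does not depend on the assumed rates.

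**If QoL and recurrence are linked.** Suppose recurrent patients deteriorate at twice the rate h. In the worked case the true 24-month rate is 1 − 0.80 × (0.80 × 0.7225 + 0.10 × 0.85 × 0.70 + 0.10 × 0.49) = 45.1%. Rule A gives 39.0% and rule B 42.2%, so rule B removes only part of the shortfall.

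**Median.** With low rates neither rule reaches 50% by 24 months. With high rates the 12-month figure under A is 0.40 + 0.18 × (1 − r12), or 53.5% to 57.1%, against 58.0% under B. The median is the 12-month visit under both rules.

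**The case against.** **The rule may not cover QoL.** IX.2 joins the QoL endpoint to SSR and OS with an as-well-as phrase, and the censoring sentence then speaks only of time-to-event criteria. A narrow reading would exempt QoL. The term for the last update is also undefined; for QoL it could mean the last questionnaire. The wording is indeed ambiguous. But time to deterioration is a time-to-event quantity on its ordinary meaning, no other section supplies a QoL censoring date, and one sentence settles the matter on either reading.

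**The event is not fully defined.** If the analysis plan counts recurrence or death as deterioration, the bias disappears and the endpoint answers a different question (53.8% in the worked case: 1 − 0.80 × 0.80 × 0.7225). This is correct. Still, the protocol does state a censoring rule, and an analysis plan that simply follows it inherits the problem.

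**Other provisions help.** The mixed model in IX.4 does not use the censoring date, but it is a separate analysis. IX.5 promises a sensitivity analysis of attrition and possible imputation. That bears on forms missed by recurrence-free patients, but it does not move the censoring date, and forms after recurrence are absent by design.

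**The effect is modest.** With 90 patients, a rate of 42% has a 95% half-width of about 1.96 × √(0.42 × 0.58 / 90) = 10 points even without censoring. No decision rule uses QoL. Both statements stand and limit the weight of the point.

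**Conclusion.** The concern holds for the 12- and 24-month deterioration rates, on the natural reading of IX.2. The downward direction follows from the rule and the collection schedule. The size, about 2 to 10 points at 24 months for 10 to 40% recurrence, rests on assumed deterioration rates, on recurrence independent of QoL and on no deaths. If QoL worsens with recurrence, the shortfall against the true rate is larger.

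A reader might infer more than the protocol supports:

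- **A delayed median.** Not shown: in these scenarios it is either not reached or falls at the same visit under both rules.
- **Mis-censoring of every time-to-event endpoint.** The argument concerns QoL only. SSR and OS have their own censoring statements in VI.7.4 and VI.7.5, and vital status continues to be collected after recurrence.
- **A distorted QoL benefit claim.** The benefit listed in I.5 concerns QoL during treatment, whereas this bias arises at 12 and 24 months.
- **An effect on the trial's conclusion.** The primary toxicity decision does not use this endpoint.

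The correction is worth making because it is cheap. It concerns a descriptive secondary endpoint.

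**What to change.** In IX.2, state that time to QoL deterioration is censored at the last completed questionnaire, or at inclusion if none follows, and not at the last update. Add a sensitivity analysis that counts recurrence or death as deterioration. It is needed because censoring at the last questionnaire stays informative if recurrence and QoL are linked. Report it as a composite, since it answers a different question from deterioration alone.

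The cost is one sentence and one further run, with no new data. Fewer patients will be at risk at 24 months and the intervals will be wider, which reflects what was actually observed.

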## STATISTICAL CONSIDERATIONS

### Estimating the number of patients needed

With a one-step Fleming plan, the calculation of the number of patients needed takes into account:

- The primary endpoint: severe toxicity at 2 years limited to 5-15%, minimum N is equal to 67 patients (unilateral,  $\alpha = 0.05$ ,  $\beta=0.10$ )
- and the secondary endpoint: 2-year local control of 80-90%, minimum N is equal to 83 patients (unilateral,  $\alpha = 0.05$ ,  $\beta=0.20$ )

In order to compensate for possible loss to follow-up, 90 patients will be included.

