### IX.1. Number of topics to include

881 To determine the number of patients needed, two objectives were considered: severe late toxicity at  
882 2 years (primary outcome) and local control rate at 2 years (secondary outcome). The experimental  
883 design follows a one-step Fleming design with no intermediate analysis due to the primary endpoint  
884 which will be evaluated at 2 years (severe late toxicity).

885 The safety and efficacy profile of hypofractionated stereotactic radiotherapy of the operative bed is  
886 expected to be equivalent to other radiotherapy techniques (brachytherapy or normofractionated  
887 IMRT) (cf 3. Rationale of the study for details). In brachytherapy, the rate of late soft tissue ulceration  
888 is around 10-20% and the rate of bone necrosis is around 5-10%. We have decided: 1/ to accept a rate  
889 of less than 5% and 2/ to reject a rate of more than 15%. With a unilateral test for significance ( $\alpha=0.05$ )  
890 with a power of 90% ( $\beta=0.10$ ), the minimum number of patients to be included is 67.  
891 Hypofractionated stereotactic radiotherapy of the operative bed will then be considered an  
892 unacceptable treatment if 6/67 patients (9%) or more have severe late toxicity (grade  $\geq 3$ ).

893 The local control rate of hypofractionated stereotactic radiotherapy is expected to be equivalent to  
894 other radiotherapy techniques (brachytherapy or normofractionated IMRT). We have decided: (i) to  
895 accept a rate of more than 90% and (ii) to reject a rate of less than 80%. With a one-sided significance  
896 test ( $\alpha=0.05$ ) with a power of 80% ( $\beta=0.20$ ), the minimum number of patients to be included is 83.  
897 A lower potency was decided for control as a secondary outcome. Hypofractionated stereotactic  
898 radiotherapy of the operative bed will then be considered an acceptable treatment if 72/83 patients  
899 (87%) or more are locally controlled at 2 years.

900 As a result of these results, and to compensate for possible loss to follow-up, a total of 90 patients  
901 will be included in this study.

902 As the primary objective of this study is estimated at 2 years, once 30 patients have been included  
903 (33% of inclusions), a review of all grade  $\geq 3$  toxicities will be communicated to the independent trial  
904 monitoring committee (IDSMC = *Independent Data and Safety Monitoring Committee*). The grade 4  

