### 933 **IX.3. Main analysis**

934 The analysis of the main objective, i.e. the rate of severe toxicity of grade  $\geq 3$  to 2 years, with its 95%  
 935 CI will be compared to 15% (with regard to the assumptions set in the context of the estimation of  
 936 the number of subjects needed). If the 95% CI does not include this rate, the trial will be considered  
 937 positive. For efficacy endpoints, 95% bilateral confidence intervals will be provided. Statistical  
 938 analysis will be performed on an intention-to-treat basis.

939 An analysis of the predictive factors of severe toxicity of grade  $\geq 3$  to 2 years will be performed. A  
 940 univariate analysis will be performed using the usual tests: Student's test or Mann-Whitney test if the  
 941 conditions of the t-test are not met (normality, and homoscedasticity studied by the Fisher-Snedecor  
 942 test) for quantitative variables and Chi2 test or Fisher's exact test for categorical variables. The  
 943 multivariate analysis will consider a logistic regression model for binary dependent variable.  
 944 Covariates will be retained based on the results of univariate analysis and their clinical relevance.

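### Local control is sized as a one-sided 5% test, but the general two-sided default in IX.2 does not exempt it, so the protocol does not say which standard governs

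*Protocol*

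**What the plan says.** **Protocol IX.1 (Number of topics to include).** For 2-year local control the sponsor will "accept a rate of more than 90% and (ii) to reject a rate of less than 80" percent. The sizing sentence opens "With a one-sided significance" and gives alpha 0.05, power 80% and a minimum of 83 patients. Treatment is to be called acceptable if 72 or more of 83 patients (87%) are locally controlled. The section explains that power was set lower here than for toxicity because local control is secondary.

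**Protocol synopsis (Estimating the number of patients needed).** It gives the same design: "minimum N is equal to 83 patients (unilateral", alpha 0.05, beta 0.20. Toxicity alone needs 67 patients, so local control is what raises the minimum to 83. Enrolment is then set at 90 to cover losses to follow-up.

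**Protocol IX.2 (Data analysis: general).** "Tests will be bilateral", with p<0.05 as the significance limit. No endpoint is exempted.

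**Protocol IX.3 (Main analysis).** "For efficacy endpoints, 95% bilateral confidence intervals will be provided". No decision is attached to these intervals. The sentences just before it, on toxicity, do attach one: the trial is positive if the 95% interval excludes 15%.

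**The concern.** Local control is the only secondary endpoint with its own acceptance rule, and it sets the sample size. Its design is one-sided at 5%. The only statement on sidedness in the analysis sections is two-sided at 5%, which in the favourable direction is about as strict as a one-sided 2.5% test. IX.2 to IX.4 neither repeat the one-sided test or the count rule nor say that IX.1 takes precedence.

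An analyst who follows IX.1 and one who follows IX.2 could then give opposite answers on the same data. The report could call the treatment acceptable beside a p-value that its own analysis section labels non-significant. If IX.2 governed, the stated power for local control would also be wrong.

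**Working it through.** **Inputs (IX.1 and synopsis).** p0 = 0.80, p1 = 0.90, one-sided alpha 0.05, power 0.80, stated N = 83, stated cutoff 72/83, enrolment 90. From IX.2: two-sided, p<0.05.

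**1. Reproduce the stated N.** Single-arm normal approximation:

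n = [(z_alpha·√(p0·q0) + z_power·√(p1·q1)) / (p1 − p0)]²

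- One-sided 5%: [(1.645 × 0.4 + 0.842 × 0.3) / 0.1]² = 82.9, rounded up to 83. This matches the protocol.
- Two-sided 5%: [(1.960 × 0.4 + 0.842 × 0.3) / 0.1]² = 107.4, rounded up to 108.

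The stated 83 is therefore a one-sided size.

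**2. Exact binomial results against 80%.** One-sided p = P(X ≥ x | n, 0.80). Two-sided p sums all outcomes no more probable than the one observed. Power = P(X ≥ x | n, 0.90) if x is the cutoff.

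| Controlled | Rate | One-sided p | Two-sided p | Power with this cutoff |
|---|---|---|---|---|
| 72/83 | 86.7% | 0.076 | 0.133 | 87.7% |
| 73/83 | 88.0% | 0.041 | 0.074 | 79.5% |
| 74/83 | 89.2% | 0.020 | 0.039 | 68.4% |
| 79/90 | 87.8% | 0.038 | 0.066 | 81.4% |
| 80/90 | 88.9% | 0.019 | 0.035 | 71.3% |

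- 73/83 and 79/90 pass one-sided and fail two-sided, on sidedness alone.
- The first counts to pass the two-sided test are 74/83 and 80/90.
- 72/83 passes the written count rule but fails an exact 5% test of either kind. That gap is not due to sidedness: as a cutoff, 72/83 has an exact one-sided alpha of 0.076.

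**3. Power by rule at a true 90%, N = 83.** Written 72/83 rule 87.7%; exact one-sided 5% cutoff (73) 79.5%; exact two-sided 5% cutoff (74) 68.4%. The normal approximation for the two-sided test gives 66.4%.

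**4. Dependence on interval method.** The lower limit of the two-sided 95% interval at 73/83 is 79.0% (Clopper-Pearson), 79.2% (Wilson) or 80.9% (Wald). Only Wald excludes 80%. At 79/90 the three limits are 79.2%, 79.4% and 81.0%, with the same split.

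**The case against.** The strongest case is that the protocol already fixes how local control is judged: a specific count rule, 72/83, tied to a one-step Fleming design. The two-sided sentence sits in a section of general defaults, directly after log-rank and Cox comparisons between groups, and reads naturally as a default for comparisons of that kind. Nothing in IX.2 to IX.4 orders a p-value for local control against 80%. Read this way, the specific rule overrides the general one and nothing conflicts. This is a fair reading and it limits the point. It does not remove it, because the protocol never states that precedence and IX.2 exempts nothing.

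Two stronger readings are tempting, and the documents do not support them.

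- A reader might infer that IX.3 itself contradicts the one-sided design by giving efficacy endpoints 95% two-sided intervals. It does not. Those intervals are only to be reported, and a two-sided 95% interval beside a one-sided design is ordinary practice.
- A reader might infer that the stated 80% power is simply lost. That follows only if the two-sided test governs. On an interval reading it also depends on the method, which the protocol does not name: a Wald interval keeps the cutoff at 73/83 and the power at 79.5%.

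It is also true that local control is secondary, that IX.2 calls the trial exploratory, and that an analysis plan is due before database freeze. These facts limit the weight of the point. But the issue is a pair of statements within the protocol that are not reconciled, not a detail left to a later document.

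**Conclusion.** The point holds as an unresolved ambiguity. Local control is sized one-sided at 5%, the general analysis rule is two-sided at 5%, and the protocol does not say which one governs a local-control test.

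With exact tests, sidedness alone changes the answer at a single count: 73 if 83 are evaluable, 79 if all 90 are. If the two-sided exact test governed, power at a true 90% would be about 68% (83 patients) or 71% (90 patients), against the stated 80%. If the count rule in IX.1 governs, there is no loss: 72/83 gives about 88% power, at an exact one-sided alpha of 0.076 instead of 0.05.

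These figures assume exact binomial tests against 80%, design rates of 80% and 90%, and a known 2-year local-control status for every patient counted.

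**What to change.** **IX.2.** Exempt the sized local-control test from the two-sided default.

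**IX.3.** State that local control is tested one-sided at 5% against 80% by the exact binomial test, with the matching bound: the one-sided 95% lower limit, which is the lower limit of a two-sided 90% exact interval. Keep the 95% two-sided interval as description.

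**IX.1.** Align the cutoff with that test. Changing IX.2 and IX.3 alone would leave 72/83 passing the count rule and failing the exact test. Choose one:

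- 73/83 (exact alpha 0.041, power 79.5%), or 79/90 (alpha 0.038, power 81%) if all 90 are evaluable.
- Keep 72/83 as the decision rule and state its exact one-sided alpha of 0.076 and power of 88%. IX.3 should then name this count rule as decisive.

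If the sponsor prefers the two-sided 5% test, restate the local-control power as about 68% at 83 patients (cutoff 74) or 71% at 90 (cutoff 80).

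The cost is wording in IX.1 to IX.3, with no added patients or data. It should be settled before results are known.
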